### Analysis of endpoints

The planned analyses are summarized in Table 2. We will use a two-tailed *p* value of 0.05 and report the 95% confidence intervals for all endpoints. In all analyses, we will control for confounders of adherence and retention [7, 48, 49]. In both primary and secondary outcomes, we will undertake per-protocol and intention-to-treat analyses.

**Table 2 Tab2:** Analysis of quantitative outcomes

Outcomes	Measure of outcomes (intervention versus control arm)	Statistical analysis
Treatment success	Proportion of patients with treatment success at six months. Odds ratio of treatment success	Logistic regression, odds ratios
Cure rates	Proportion of patients cured of TB; odds ratio of TB cure	Logistic regression, odds ratios
Treatment completion	Treatment completion rate; odds ratio of treatment completion	Logistic regression, odds ratios
Retention in care	Hazards of attrition in the intervention versus control; Cumulative attrition at six months	Cox’s proportional hazards model, log-rank test
Adherence to TB medicines	Mean adherence rates (proportion of TB medicines)	Mann-Whitney U test and Poisson regression
Appointment keeping and punctuality	Proportion of patients who keep an appointment; Proportion of patients with early, prompt, and late visits	Ordered logistic regression
Drug-resistant TB rates	Proportion of patients with rifampicin-resistant TB	Logistic regression, odds ratios
Call success rates (2,4, and 6 months)	Proportion of successful calls	*t* test

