### Analysis of quantitative endpoints

Logistic regression will be used to determine the adjusted odds ratio for TB cure and treatment completion in the intervention arm versus control arms. We will also determine the predictors of TB cure overall and in both arms. The final model will adjust for age, sex, bacterial load, HIV status, TB site, and symptoms at baseline. We will also determine and compare attrition in the two study arms using the Cox proportional hazards model. We will compute the crude and adjusted hazard rates of attrition in the intervention and control arms. The log-rank test will be used to test for differences in attrition between the study arms. Tests for the Cox proportional hazard assumption will be done graphically using Schoenfeld residuals. The model will adjust for age, sex, Karnofsky score at baseline, HIV status, transport costs, distance from the health facility, TB site, and socioeconomic covariates.

We will compare the mean adherence rates (proportion of TB medicines taken as evidenced by TB card) at 6 months in the intervention and control arms. We will treat adherence as a continuous covariate and compare the median adherence between the intervention and control arms. To compare appointment keeping, we will use ordinal logistic regression to determine the adjusted odds ratios of missed, late, and prompt visits (early used as a reference group). In the sensitivity analysis, Poisson regression will be used to compare the number of missed visits and treatment doses in the intervention and control arms. The models will adjust for age, sex, employment, distance from the health facility, and HIV status. We will use chi-square to compare the proportions of patients with MDR-TB between the two study arms. Additionally, logistic regression will be used to determine the crude and adjusted odds ratios of MDR-TB in the intervention and control arms. Finally, as a proxy for the uptake of intervention and fidelity, we will determine the proportions of successful and dropped and received calls at three different (2, 4, and 6 months) to determine patient exposure and acceptance of the intervention through the study treatment period.

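### Poisson regression as named would give error bars that are too narrow for missed doses, and the adherence plan contradicts itself on summary, time points and the status of that model

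*Protocol article*

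**What the plan says.** All references are to the protocol article.

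- **Model.** Analysis of quantitative endpoints, under the label of a sensitivity analysis, says that "Poisson regression will be used to compare the number of missed visits and treatment doses in the intervention and control arms". Covariates listed there are age, sex, employment, distance and HIV status. Neither this section nor Table 2 names an offset, a dispersion term or a variance estimator.
- **Table 2** (Analysis of endpoints): the adherence measure begins "Mean adherence rates (proportion of TB medicines" and the method is "Mann-Whitney U test and Poisson regression". The table does not call the Poisson model a sensitivity analysis.
- **Summary.** Analysis of quantitative endpoints first says "We will compare the mean adherence rates (proportion of TB medicines taken as evidenced by TB card) at 6 months". The next sentence says the trial will "compare the median adherence between the intervention and control arms".
- **Time points.** Trial endpoints has adherence compared at months 2 and 6. The analysis section names 6 months only.
- **General rules.** Analysis of endpoints calls for control of confounders in every analysis and sets the level: "We will use a two-tailed *p* value of 0.05". It also promises to "report the 95% confidence intervals for all endpoints".
- **Follow-up.** Participant withdrawal and post-trial care says data collection ends when a participant withdraws. Sample size determination assumes 11.8% lost to follow-up.

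**The concern.** Poisson regression sets the variance of a count equal to its mean. A patient's missed doses are a sum over many days, and patients differ in how well they take treatment, so the variance of the total can far exceed its mean. The model-based intervals are then too short and the test rejects too often.

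The label "sensitivity analysis" does not remove the problem. Confounder control is required throughout, a Mann-Whitney test takes no covariates, and no other adjusted adherence model is named. The Poisson model would therefore supply the adjusted adherence estimate and its interval. Adherence is a secondary objective and part of the proposed mechanism of the intervention, so a spurious difference could mislead.

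The second problem is in the printed text. Mean and median adherence can disagree when most patients are near 100%: medians can be equal while means differ. A Mann-Whitney test strictly tests neither. With two summaries, two sets of time points and two statuses for one model, the choice of result to report stays open until the data are seen.

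**Working it through.** **Plan's own figure.** The article gives no variance, dispersion or power figure for adherence, missed visits or missed doses, so there is none to reproduce. The total of 274 is for the primary endpoint.

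**Inputs**
- Patients: 137 per arm, 11.8% lost, so 137 × 0.882 ≈ 121 evaluable per arm (Sample size determination).
- Doses due, D: 6 months of treatment (Control arm and the standard of TB care in Uganda). Daily dosing is assumed: 24 × 7 = 168 or 6 × 30 = 180.
- Visits due, V: two in the first month, then one in each of months 2 to 6, so about 7 (same section).
- Missed fraction m and between-patient ICC ρ: assumed, since the article gives neither.

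**Formulas.** For a beta-binomial count the variance is D·m(1−m)[1+(D−1)ρ]. The Poisson variance is D·m. Their ratio is φ = (1−m)[1+(D−1)ρ], and the model-based standard error is too small by √φ. Type I error at nominal 5% is about 2[1−Φ(1.96/√φ)]. The between-patient SD of the true missed fraction is √(ρ·m(1−m)).

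**Missed doses, D = 168, m = 0.10**

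| ρ | SD of missed fraction | φ | √φ | Type I error |
|---|---|---|---|---|
| 0.01 | 3.0 points | 0.9 × 2.67 = 2.40 | 1.55 | 0.21 |
| 0.02 | 4.2 points | 0.9 × 4.34 = 3.91 | 1.98 | 0.32 |
| 0.05 | 6.7 points | 0.9 × 9.35 = 8.42 | 2.90 | 0.50 |

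Simulation of 4,000 null trials per scenario, with 121 per arm and D = 180, agrees. Type I error was 0.053 at ρ = 0.001 (an SD of about 1 point), 0.22 at 0.01 and 0.52 at 0.05. At ρ = 0.01 it was 0.20 to 0.22 for m from 0.05 to 0.20. With a robust variance it stayed between 0.045 and 0.061 in every dose and visit scenario.

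**Missed visits, V = 7**
- m = 0.10: φ = 0.9 × 1.06 = 0.95 at ρ = 0.01, 0.9 × 1.3 = 1.17 at 0.05, and 0.9 × 1.6 = 1.44 at 0.1. Simulated type I error was 0.048, 0.065 and 0.10.
- m = 0.30, ρ = 0.05: φ = 0.7 × 1.3 = 0.91, type I error 0.04, slightly conservative.
- m = 0.10, ρ = 0.3: φ = 0.9 × 2.8 = 2.52, type I error 0.22. Only strong clustering makes this serious.

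**Unequal exposure.** Assume loss at mid-treatment of 11.8% in one arm and 5% in the other. Mean exposure is 1 − 0.118/2 = 0.941 against 1 − 0.05/2 = 0.975. Without an offset the spurious rate ratio is 0.975/0.941 ≈ 1.04.

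**The case against.** - **Silence is not a decision.** The article says only Poisson regression. An offset or a robust variance may stand in the full protocol or an analysis plan, neither of which is shown. This stands in part: a reader might infer that uncorrected Poisson will be run, and the article does not say so. But it does name the model, and for missed doses the standard form of that model gives wrong error bars. The same section specifies a check of the proportional hazards assumption and none for dispersion.
- **Overdispersion is assumed.** True, and near ρ = 0.001 the test holds its level. That, however, requires almost identical adherence in all patients. The article itself points to heterogeneity: it cites loss to follow-up of 3.5% in urban and 16.6% in rural settings, and it recruits from urban, peri-urban and rural sites.
- **The outcome is ambiguous.** The phrase could mean doses taken. Then φ = m[1+(D−1)ρ], which for D = 168 and m = 0.10 is 0.43 at ρ = 0.02 and 0.94 at 0.05, so there is no inflation over that range. This stands, and is a reason to name the count.
- **The stakes are limited.** Treatment success is analysed by logistic regression, and appointment keeping mainly by ordered logistic regression. This stands.

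The contradictions between sections are conflicts in what is printed, and no unseen document explains them away.

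**Conclusion.** The point holds for missed doses and for the internal contradictions. For missed doses, model-based Poisson inference gives a type I error of about 20% once the true missed fraction varies between patients with an SD of 3 percentage points. At an SD of 6.7 points it is about 50%. Both figures assume daily dosing, 10% missed and beta-binomial variation.

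Three stronger readings are not supported:
- A false difference between identical arms most of the time: this needs an ICC above about 0.05, and no dispersion figure is given.
- Equally poor error bars for missed visits: with about 7 due, the inflation is mild at low correlation and can reverse.
- Serious bias from early drop-out: the example above gives a rate ratio of only about 1.04.

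The mean/median, time-point and main-versus-sensitivity conflicts need no assumption. The primary endpoint is unaffected.

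**What to change.** - For missed-dose and missed-visit counts, use Poisson regression with robust (sandwich) standard errors, or a negative binomial model, with an offset of log(doses due) or log(visits due). State that the count is doses missed, and how doses due are counted for patients who withdraw.
- Name one adherence summary, for example the difference between arms in the mean proportion of doses taken, with a robust or bootstrap 95% confidence interval. Keep the Mann-Whitney test as support.
- Make Trial endpoints, Table 2 and Analysis of quantitative endpoints agree on the summary, the time points (months 2 and 6, or 6 only) and whether the Poisson analysis is main or sensitivity.

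The cost is a change of wording and, for missed doses, wider confidence intervals. No new data and no change to the sample size are needed.

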### Research objectives

The primary objective of this study is to determine the impact of an IVRT software (CFLU-TB) on treatment success in patients receiving treatment at public facilities in Uganda. The secondary objectives were as follows:
To compare TB cure rates (six months) in patients with microbiologically diagnosed TB in the intervention and control arms.To compare treatment completion (six months) in patients clinically diagnosed with TB in the intervention and control arms.To determine the effect of enhanced TB treatment support with CFLU-TB on retention at 2 and 6 months in patients receiving TB treatment.To assess the perception of patients’ care providers (treatment buddies) and other stakeholders about CFLU-TB.To determine the cost-effectiveness of the intervention.To compare adherence rates between patients in the intervention arm and control arms.To determine the effect of CFLU-TB on adherence to clinic appointments.To compare knowledge about TB/HIV in patients enrolled in the intervention and control arms.To determine Drug-resistant TB rates in the intervention and control arms.To determine the uptake of the CFLU-TB tool in patients and their care providers (treatment buddies).

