#### Exclusion criteria

Inability to use a basic feature phone or presence of a clinical condition that interferes with appropriate use of the mobile phone for voice calls (e.g., deafness, severe cognitive impairment)Ongoing participation in another interventional study that the investigator believes will interfere with study procedures or assessment of the outcomes of this study.Patients who are critically ill.Patients with drug-resistant TB (Rifampicin resistant, Multi-drug resistant, and extensive drug-resistant TB).Patients with TB meningitis or osteoarticular TB.Any other clinical condition that, in the opinion of the site investigator, would make the participant unsuitable for the study or unable to comply with dosing requirements.

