### Trial endpoints

The primary endpoint is treatment success (at 6 months): treatment success is a composite outcome, comprising treatment completion and cure in patients with clinically and bacteriologically diagnosed TB, respectively. It is a robust and agreed indicator of treatment success in TB programs. In patients with bacteriologically diagnosed TB, cure is defined as having a negative sputum test in the last month of treatment and on at least one previous occasion [47]. For clinically diagnosed patients, completion entails 6 months of therapy. The denominator for each arm will be the number of patients enrolled. At the same time, the numerator is the sum of bacteriologically and clinically diagnosed patients with cure or treatment completion, respectively.

This RCT also has several secondary endpoints. First, we will determine the TB cure rates in patients with microbiologically diagnosed TB. Second, we will determine treatment completion for patients clinically diagnosed with TB in the two arms: Third, retention rates will be determined and compared between the study arms. Patients will be deemed to be actively engaged in care if they attend a clinic visit within one month of a scheduled appointment. Additionally, we will compare appointments. We will categorize visits as “early,” if they present before an appointment, “prompt” if they show up within three days after the appointment date, “late” if they present after three days but within 30 days of a scheduled appointment and missed if patients do not show up at all or present after 30 days. Fourth, we will determine the incremental costs per additional DALY averted per percentage point increase in treatment success in the intervention versus the control arm. In addition, we will compare adherence rates at months 2 and 6. Depending on the availability of drug susceptibility tests, we will compare the rates of MDR-TB. To understand the impact of the intervention on the treatment outcomes and the potential for adoption and scaling of the intervention, we will explore the perceptions and experiences of patients and care providers towards the MHI. Finally, we will determine the uptake and adherence to the intervention. We will consider the successful receipt of a reminder as a proxy for the utilization of the technology. Therefore, we will determine the proportion of successful calls in the intervention and control arms.

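### The drug-resistance endpoint is rifampicin-resistant TB in Table 2 but MDR-TB in the text, and the adjusted logistic model fixed for it would rest on too few events

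*Protocol article*

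**What the plan says.** The protocol article describes this endpoint in four places.

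- **Research objectives:** "To determine Drug-resistant TB rates in the intervention and control arms", with no type of resistance named.
- **Trial endpoints:** "Depending on the availability of drug susceptibility tests, we will compare the rates of MDR-TB".
- **Analysis of endpoints, Table 2:** the row on drug-resistant TB is measured as "Proportion of patients with rifampicin-resistant TB", and the only method listed is logistic regression with odds ratios.
- **Analysis of quantitative endpoints:** "We will use chi-square to compare the proportions of patients with MDR-TB between the two study arms". In addition, "logistic regression will be used to determine the crude and adjusted odds ratios of MDR-TB in the intervention and control arms". Shortly before, for the appointment and missed-dose models, the section states: "The models will adjust for age, sex, employment, distance from the health facility, and HIV status".

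The Exclusion criteria remove "Patients with drug-resistant TB (Rifampicin resistant, Multi-drug resistant, and extensive drug-resistant TB" at entry. Analysis of endpoints requires control for confounders in all analyses. The Sensitivity analysis section repeats every secondary quantitative endpoint by HIV status, TB type and gender.

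**The concern.** Rifampicin-resistant TB and MDR-TB are not the same outcome. The protocol's own exclusion list names them as separate categories. They also come from different tests. Study settings ties rifampicin resistance to GeneXpert, which Table 1 schedules in both arms at months 5 and 6. The MDR-TB comparison is made conditional on susceptibility tests being available. Two numerators and two tested denominators could thus be reported under one endpoint, with nothing in the article to say which is meant.

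The second problem is the adjusted model. The trial excludes known resistance, follows patients for six months and enrols 274. A multivariable logistic regression on the few resistance events left can give an unstable odds ratio, or one that is zero or infinite if an arm has no events. An odds ratio of that kind, printed beside the other adjusted results, would look more informative than it is.

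**Working it through.** **Inputs from the protocol**
- 274 patients, 137 per arm; assumed loss to follow-up 11.8% (Sample size determination).
- Two-sided 0.05 (Analysis of endpoints).
- Five covariates: age, sex, employment, distance, HIV status (Analysis of quantitative endpoints). I assume that this set also applies to the resistance model. With the arm term that is at least 6 coefficients, and more if employment has several categories.

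**Input not in the protocol**
- The resistance rate at follow-up. I assume 0.5% to 5%, equal in both arms and with everyone tested. There is no stated event count or power for this endpoint to reproduce.

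**Step 1. The definitions side by side**

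| Place | Outcome | Method |
|---|---|---|
| Research objectives | Drug-resistant TB, type not given | none given |
| Trial endpoints | MDR-TB, if tests are available | comparison of rates |
| Table 2 | Rifampicin-resistant TB | Logistic regression |
| Analysis of quantitative endpoints | MDR-TB | Chi-square, plus crude and adjusted logistic regression |

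The outcomes and the methods both differ.

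**Step 2. Expected events**

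With rate p and n = 137 per arm:
- expected total = 2np
- chance that at least one arm has no events = 1 − [1 − (1 − p)^n]²
- events per coefficient = 2np / 6

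| Assumed rate | Expected events | At least one arm with none | Events per coefficient |
|---|---|---|---|
| 0.5% | 1.4 | 75% | 0.2 |
| 1% | 2.7 | 44% | 0.5 |
| 2% | 5.5 | 12% | 0.9 |
| 3% | 8.2 | 3% | 1.4 |
| 5% | 13.7 | 0.2% | 2.3 |

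Example at 1%: 2 × 137 × 0.01 = 2.74. 0.99^137 = 0.252, and 1 − (1 − 0.252)² = 0.44.

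With 121 per arm (137 × 0.882) the expected totals run from 1.2 at 0.5% to 12.1 at 5%. The rough guide of ten events per coefficient would need 60 events, and 60/274 = 22% of patients.

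**Step 3. Is the chi-square test itself at fault?**

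In individual sparse tables it disagrees with Fisher's exact test. For 0 v 4 events, uncorrected chi-square gives p = 0.044 and Fisher 0.122. For 0 v 5 the values are 0.024 and 0.060. The proper check is the type I error, summed over all tables at equal true rates with 137 per arm:

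| Assumed rate | Uncorrected chi-square | Fisher |
|---|---|---|
| 0.5% | 0.5% | 0.01% |
| 1% | 2.5% | 0.1% |
| 2% | 4.5% | 1.0% |
| 3% | 4.4% | 1.7% |
| 4% | 4.6% | 2.1% |
| 5% | 4.8% | 2.3% |

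Chi-square stays below 5% at every rate, and also with 121 per arm. The protocol does not rule out a continuity correction, which gives p = 0.131 for 0 v 4 and 0.071 for 0 v 5.

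**The case against.** The strongest reply is that the resistance rate is assumed, not documented, and that this is one conditional secondary endpoint whose dependence on test availability the protocol states openly. That is fair, and it is why a range is shown. The contradiction in the definition does not depend on any rate, and the adjusted model is short of events across the whole range.

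Four stronger readings are tempting, and the documents do not support them.

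- **That chi-square is invalid here.** Its type I error does not exceed 5% at any of the rates examined. Fisher's larger p-values reflect its conservatism. Choosing Fisher is a preference, not the correction of an error.
- **That only newly acquired resistance can count.** Study settings describes rifampicin testing for sputum-positive patients, and the Inclusion criteria also admit clinically diagnosed patients. Resistance missed at entry could add events.
- **That the logistic model cannot be fitted.** At 2% the chance of a zero-event arm is 12%, so the crude odds ratio would often be finite. The adjusted one would still be poorly supported.
- **That susceptibility tests are not planned.** Table 1 lists culture and susceptibility testing in both arms at months 0, 2, 5 and 6. All but month 5 carry a footnote tying it to national guidelines.

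It is also fair to object that rifampicin resistance does not by itself settle the denominator. If the result is read only in patients who are still sputum-positive, few will have one at month 5 or 6. The fix has to deal with that.

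**Conclusion.** The point holds in two parts. First, one secondary endpoint has two incompatible definitions and two sets of methods. This follows from the text alone. Second, the adjusted logistic regression fixed for it is not supportable: 1.4 to 13.7 events in total are expected at assumed rates of 0.5% to 5%, at most about 2.3 per coefficient. The second part rests on the assumed rates, on full testing of 137 per arm, and on the five listed covariates applying to this model. Incomplete testing or further stratification would thin the events more. The importance is minor: neither the primary analysis nor the sample size of 274 is touched.

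**What to change.** 1. Use one definition in Research objectives, Trial endpoints, Table 2 and Analysis of quantitative endpoints. Rifampicin resistance on GeneXpert at month 5 or 6 matches Table 2 and uses a test already scheduled in both arms.
2. State the denominator: all randomised patients, showing per arm how many were tested and how many had a rifampicin result.
3. Report MDR-TB descriptively, among those with a susceptibility test.
4. Report counts per arm with exact 95% confidence intervals and a single prespecified unadjusted comparison. Chi-square may stay if named as that comparison, with any continuity correction stated.
5. Drop the adjusted logistic model, or replace it with a penalised (Firth) or exact model. Record this as an exception to the rule that all analyses control for confounders.

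The cost is wording in four places and the loss of a conventional adjusted estimate for one secondary endpoint. No visit, test or patient is added.
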